### Intervention group

As shown in Figure 1, each subject in the intervention group will receive four Zoom video conference sessions and four telephone calls conducted by a nurse case manager (NCM) and a community worker (CW) who will be supervised by the NCM during the 3-month programme. In the first Zoom meeting, the NCM, who has more than 20 years of community elderly care experience, will comprehensively assess the health and social problems of the subjects using the Omaha System. The Omaha System is a holistic assessment tool that evaluates environmental, physiological, psychosocial, and health-related behaviours, and covers 42 problems [35]. For example, the problems of sanitation and residence belong to the environmental domain, while the problems of respiration and cognition belong to the physiological domain. After the problems are identified, the NCM will empower the subjects to set realistic goals; identify facilitators and barriers that may promote or hinder the achievement of these goals; provide health and self-care education; and build self-efficacy by verbal encouragement, recalling previous effective self-care strategies, and taking note of the beneficial effects of adopting self-care behaviour [28]. After the first Zoom meeting, the CW will follow-up with the subjects, under the supervision of the NCM, and evaluate their progress in achieving their goals. The CW will encourage the subjects to work on their self-care goals and maintain self-care behaviour and will provide information about the health and social activities that are organised by the community centre. To reduce the risk of infection during the coronavirus (COVID-19) pandemic, Zoom meetings and telephone calls will be used as the delivery channels.

**Fig. 1 Fig1:**
[figure not shown]
Study flow of the programme

When deemed necessary, the NCM will refer the subjects to one of the health and social care team members, such as a general practitioner, traditional Chinese medicine practitioner, or social worker. The referral guidelines and protocols will be co-developed by the health and social care team. The roles and responsibilities of each member in the team will be included in the protocols with the full support of the health and social care sectors. In addition, monthly interdisciplinary care conferences will be organised to allow the subjects to discuss their progress, address their concerns, and modify and revise their care goals.

To facilitate the implementation of the programme in the community centre, the research team has held several meetings with the staff in the community centre to gain initial agreement for collaboration and to discuss the potential benefits of the programme to the community centre and the older adult members. A formal presentation was also given to inform the managers and staff at the community centre about the study rationale, timeline, roles and responsibilities of the staff, recruitment process, and referral criteria. The research team members will be informed that there will be telephone support should they encounter difficulties during the study process.

The research team has gathered feedback from the centre managers and staff on the logistics of the programme and from older adults on their preferences so that the programme can be integrated into one of the existing services provided by the community centre. To prevent research design failure, the research team will provide training to all key stakeholders, including health and social care providers and community centre managers and staff.

Before the commencement of the programme, the research team will organise a 3-day training workshop for the NCM and the centre service providers, such as the administrative staff, social workers, and CWs. The training content will include the implementation process, theoretical knowledge and practical skills, documentation processes, and the referral guidelines and support system. Didactic lectures and role playing will be used to ensure that the service team members understand and are able to apply what they have learned in a case scenario. To ensure that the centre staff are competent at applying what they have learned in the programme, the NCM will use the Omaha System to conduct a comprehensive assessment, identify any problems, and provide interventions in a simulated case according to the validated protocols. In addition, the centre staff will be required to complete and pass a post-training competence test to confirm that they have mastered the knowledge required for the subjects’ recruitment procedure.

Appropriate policies and sufficient funding are important for sustaining a programme in the community. This programme will not have the capacity to change policy, but the team will capitalise on the opportunities provided in the current policy directives to work with the social service sector to promote health in the community. In recent years, the Hong Kong government has embraced the importance of primary healthcare services and has provided support and funding to non-governmental organisations to address the health and social needs of citizens.

### Control group

Subjects in the control group will receive a monthly social telephone call from a trained research assistant. The purpose of the call will be to control the possible social effects (that is, a person will have a better social health when someone is regularly calling or caring about the person) of the intervention. When subjects have concerns about their health or have social problems, the RA will suggest that the subjects seek help from their general practitioner.

### Outcome measures

RE-AIM [30] will be adopted as the evaluation framework of the programme. Of the five dimensions included in the RE-AIM framework, only effectiveness and maintenance outcomes will be collected from both the intervention and control groups. The outcomes of the other three dimensions—reach, adoption, and implementation—will only be collected from subjects in the intervention group.

To determine whether the programme reaches the target population, the recruitment rate and subject characteristics will be collected. The recruitment rate will be calculated by dividing the total number of subjects recruited by the total number of eligible subjects in the member list of the community centre.

Since this is a pilot study, we can only measure the effectiveness outcomes if such data can be collected. The Chinese version of the General Self-Efficacy Scale will be used to measure self-efficacy level. This scale has been validated in a Chinese population and has been shown to have good validity and reliability [36]. Version 2 of the 12-item Short Form Health Survey will be used to measure quality of life [37]. This scale measures various aspects of physical and mental health, from which physical and mental component scores will be calculated. It has been widely used, with good validity and reliability [37]. The total number of unscheduled general out-patient department, general practitioner, and emergency room visits and hospital admissions and the total number of attendances at health services will comprise the health service utilisation outcomes in this study. Health service utilisation information will be collected by the subjective reporting of the subjects and will be confirmed by examining the medical and attendance certificates. This data collection protocol has been shown to have good reliability [8].

We will explore the programme adoption by using semi-structured group interviews with the providers (i.e. the social workers and the NCMs), the involved centre staff members, and eight participants (i.e. 20% of the intervention group participants). In the interviews, the research assistant will explore the interviewee’s perceptions on the facilitating factors of and barriers to program adoption in the community centre. In addition, the research assistant will also audio-record and transcribe the conversation to examine the logistic and feasibility of the programme during the interdisciplinary care conferences.

The extent to which the intervention is implemented as intended will be analysed using a performance checklist that records each step of the implementation process of the study. The checklist will be designed and completed by the PI, who will not be involved in implementing the intervention.

The maintenance effects of the intervention will be measured by repeating the measurement of effectiveness outcomes at three months following the completion of the intervention if such data can be collected.

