**Methods:**

This study will use a hybrid effectiveness-implementation design. During the 3-month programme, subjects in the intervention group will receive four Zoom video conference sessions and four telephone calls conducted by a health-social service team that will include a nurse case manager, community workers, general practitioners, a Chinese medicine practitioner, and social workers. Subjects in the control group will receive a monthly social telephone call from a trained research assistant to rule out the possible social effect of the intervention. The reach, effectiveness, adoption, implementation, and maintenance framework (i.e. RE-AIM framework) will be used to evaluate the implementation and effectiveness outcomes. Of the five dimensions included in the RE-AIM framework, only effectiveness and maintenance outcomes will be collected from both the intervention and control groups. The outcomes of the other three dimensions—reach, adoption, and implementation—will only be collected from subjects in the intervention group. Data will be collected pre-intervention, immediately post-intervention, and 3 months after the intervention is completed to evaluate the maintenance effect of the programme.

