### Objectives

To evaluate the process of implementing a nurse-led HSPP programme in a community centre, which will include the aspects of the following: *Reaching* into the target population, potential *Effectiveness* of the programme when compared to a monthly social telephone call, *Adoption* by the staff and participants, *Implementation* fidelity, and *Maintenance* over time. Specifically, these aspects are defined as follows:i)Reach: recruitment rate of the programme.ii)Potential effectiveness: self-efficacy, quality of life (QoL), health service utilisation (i.e. the total number of unscheduled general out-patient department, general practitioner, and emergency room visits and hospital admissions and the total number of attendances at health services).iii)Adoption: perceptions on the facilitating factors of and barriers to program adoption in the community centre.iv)Implementation: fidelity of the programme.v)Maintenance: sustained programme effects at 6 months.

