A staff in the centre who will not involve in recruitment and the project will provide a member list to the research team. A trained research assistant (RA) will screen the member list and make sure the potential subjects will fit for the inclusion and exclusion criteria before making phone calls to them. After briefly introduce the programme to potential subjects through phone call, the RA will arrange a home visit with them to fully explain the procedure of the programme and obtain their consent forms. The RA will collect the baseline data of those who agree to participate. After successfully collecting their data, the RA will call the principal investigator (PI) of the research team for group randomisation. The subjects will be randomly assigned in a 1:1 ratio to either the intervention group or control group. Random group assignments will be generated by the PI using Research Randomizer software (i.e. 1 = intervention group; 2 = control group). These group assignments will then sealed in envelopes and opened sequentially by the PI after receiving the call from the RA. The RA and the community centre staff, but not the PI or the healthcare providers, will be blinded to the group assignments. The PI will neither involve in recruitment process nor data collection. To prevent contamination between the intervention and control groups within the centre, strategies such as clearly communicate the procedures and interventions specific to each group and provide ongoing reminders throughout the study, maintain confidentiality regarding group assignments, and implement regular monitoring and supervision of the study activities will be adopted.

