### Sample size

Given that this is a pilot implementation study, the sample size will follow the rule of thumb of a minimum of 30 in each group [34]. As a previous study using a health-social service partnership programme for community-dwelling older adults had an attrition rate of approximately 15% [8], we will assume a 20% drop-out rate in this study. Therefore, a sample size of 36 will be needed for each group, for a total of 72 subjects in the two groups.

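### Reach, the first-listed objective, is inconsistently and poorly defined: two rules for who is counted differ by a factor of two, and the denominator mixes willingness to join with list size

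*Protocol article*

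**What the plan says.** The Objectives section lists Reach first: "Reach: recruitment rate of the programme". Outcome measures gives the formula, "dividing the total number of subjects recruited by the total number of eligible subjects in the member list of the community centre", and adds subject characteristics as further evidence on Reach.

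The opening paragraph of Outcome measures restricts the source of these data: "reach, adoption, and implementation—will only be collected from subjects in the intervention group". The Methods part of the abstract says the same of these three dimensions: "will only be collected from subjects in the intervention group".

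The section on study setting, subjects and recruitment strategies gives the sequence. Centre staff supply a member list. The research assistant (RA) is to screen it and "make sure the potential subjects will fit for the inclusion and exclusion criteria before making phone calls to them". A phone call, a home visit with consent, and baseline data collection follow, and only then 1:1 randomisation. Eligibility includes an HK-MoCA score of at least 22, smartphone use, Internet coverage where the person lives, and staying in Hong Kong for the coming three months.

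Sample size states that "a sample size of 36 will be needed for each group, for a total of 72 subjects in the two groups". The article gives neither the size nor the contents of the member list.

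**The concern.** There are three separate difficulties, of unequal strength.

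- **Who is counted.** Recruitment is complete before anyone has an arm. A recruitment rate taken only from the intervention arm is therefore not the rate that the formula describes, and eligible members who decline can be assigned to neither arm.
- **What the rate measures.** The numerator has a planned size, while the denominator is every eligible member on the list, including any who were never approached. If enrolment fills before the list is exhausted, the result says how long the list is and not how readily members join.
- **Whether the denominator can be known.** Eligibility is to be settled from the list before any call, yet some criteria need a test or a question to the member.

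At stake is whether the pilot's first objective yields one interpretable figure. Two analysts following different sentences of the same section would report rates that differ by a factor of two. A reader could also take a low coverage figure for poor acceptability.

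**Working it through.** **The plan's own figure.** Sample size starts from 30 per group and assumes 20% drop-out. 30 × 1.20 = 36 per group, and 2 × 36 = 72, so the stated figures are reproduced. They set the planned numerator of Reach. The article states no value of Reach and no number eligible. Below, E is the number of eligible members, and every value of E is an assumption.

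**1. The two rules for the numerator.** All recruited: 72/E. Intervention group only: 36/E. The ratio is 72/36 = 2 at any E.

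| E (assumed) | Both arms, 72/E | Intervention only, 36/E |
|---|---|---|
| 100 | 72.0% | 36.0% |
| 200 | 36.0% | 18.0% |
| 300 | 24.0% | 12.0% |
| 500 | 14.4% | 7.2% |
| 1000 | 7.2% | 3.6% |

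**2. Sensitivity to willingness.** Take E = 500 and let enrolment fill to 72. If a proportion a of those approached accept, 72/a members must be approached.

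| Acceptance a (assumed) | Approached, 72/a | Rate by the formula, 72/500 | Rate among those approached |
|---|---|---|---|
| 30% | 240 | 14.4% | 30% |
| 50% | 144 | 14.4% | 50% |
| 80% | 90 | 14.4% | 80% |

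The formula returns one value for three very different levels of acceptance. This needs E above 72 and full enrolment. If every eligible member is called and fewer than 72 join, the formula does reflect willingness.

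**3. Sensitivity to criteria that the list does not show.** Suppose that 300 members look eligible on the list and a fraction f of them would fail a criterion not recorded there. The rate among the truly eligible is 72/[300 × (1 − f)].

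- f = 0: 72/300 = 24.0%
- f = 10%: 72/270 = 26.7%
- f = 50%: 72/150 = 48.0%

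Both 300 and the range of f are assumed. The calculation shows only that the answer depends on when and how eligibility is established.

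**The case against.** Recruited divided by eligible is an ordinary recruitment rate. The conceptual framework section describes the dimension as reach into the target population, and on that reading eligible members who were never called are indeed not reached. Coverage of the list is therefore a legitimate quantity, and acceptance among those approached is a different one. This stands, and it is why both should be reported.

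The article does not say that calling stops at 72 or that eligible members go uncalled, and it does not describe the list. The second difficulty is thus conditional. The third is an inference, though a strong one, because no source for a cognitive score or travel plans before the call is described.

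The formula refers to the total recruited, so one may argue that the specific sentence overrides the general one. That is the likely intention, but the restriction appears in both the abstract and the main text, and the article does not say which rule governs.

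A reader might infer three stronger things that the document does not support:

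- **That Reach has been miscalculated.** No value has been calculated. The fault lies in the definition.
- **That control-arm characteristics will be lost.** Baseline data are collected from everyone who agrees, before allocation, so they will exist for both arms.
- **That the recruitment rate is the main input to the planned six-centre stage.** The Discussion ties that stage to facilitators, barriers and implementation strategies, and no stated decision depends on Reach.

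**Conclusion.** The contradiction over who is counted is established from the text alone. It is worth a factor of two, 72 against 36 in the numerator at full enrolment, whatever the length of the list.

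The insensitivity to willingness holds if more than 72 members are eligible and enrolment reaches the planned 72. Filling the sample is what the plan aims for, but the list size is unknown. The doubt about the denominator is a reasonable inference from the eligibility criteria and the stated order of screening. It is not something the article says.

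None of this affects the comparison of effectiveness outcomes between the arms. The definition should be corrected because Reach is a stated objective, its formula is given in full in the article, and the repair is nearly free.

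**What to change.** 1. Remove Reach from the intervention-only sentence in the abstract and in Outcome measures, and count recruited subjects of both arms.
2. Keep coverage of the list, and report beside it an acceptance rate with a 95% CI: the number consenting divided by the number contacted and not found ineligible.
3. Keep members who decline before HK-MoCA is done in that denominator, labelled as eligibility unknown. Dropping them would raise the rate. Give a sensitivity figure restricted to those confirmed eligible; the two figures then show how much the unknowns matter.
4. Reword the recruitment section so that the list is used only for the criteria it holds, and the rest are confirmed at the call or home visit.
5. Have the RA log each member as listed, called, reached, excluded (with reason), declined (before or after eligibility was known) or consented.

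The cost is a few changed sentences and a short contact log kept by the RA, who already makes the calls. The log must start with the first call, because calls that were not recorded are hard to reconstruct later.

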### Data analysis

Data will be analysed using Statistical Package for Social Sciences version 26 software (SPSS Inc., Chicago, IL, USA). Descriptive statistics will be calculated, and the distributions of the continuous variables will be examined for normality and homogeneity of variance.

Independent *t*-test will be used to analyse the differences between two groups, while repeated measures ANOVA will be adopted to measure the within-group differences. Intention-to-treat analysis will be used as the primary analysis method. Intervention effects will be reported as model-based means (95% confidence interval [95% CI]) and a *p*-value (level of significance). A significant result will be indicated by a *p*-value of less than .05 for a two-tailed test.

The principles of thematic analysis will be used in a deductive manner to analyse the qualitative data collected in the semi-structured interviews. One of the research team members will audio-record and transcribe the interviews for the team to examine the raw text and identify relevant themes. The team will discuss the text and construct a framework for analysis using codes and categories. All discrepancies will be resolved by consensus. The study will employ the framework that was proposed by Lincoln and Guba to ensure trustworthiness [38]. This framework encompasses four constructs: credibility, transferability, dependability, and confirmability. To establish credibility, we will utilise probes, prompts, and an iterative mode of questioning during the interviews. To enhance transferability, we will provide a comprehensive description of the study processes and emerging findings, enabling readers to assess the applicability of the findings to their own contexts. To ensure dependability, detailed documentation of the entire research process will be maintained and emphasised in the manuscript. To achieve confirmability, only participants who meet the eligibility criteria will be included in the interviews. The research team engage in discussions with subjects to validate the interpretations of the study findings. Additionally, involving native speakers who are also fluent in English and seeking ongoing consultation with the wider research team contribute to the rigorous execution of the study.

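### Health service utilisation is compared between groups by an unadjusted t-test although it is also measured at baseline, which gives away precision but does not bias the result

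*Protocol article*

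**What the plan says.** Under Outcome measures, the protocol article defines two utilisation counts. One is "The total number of unscheduled general out-patient department, general practitioner, and emergency room visits and hospital admissions". The other has no such restriction: "the total number of attendances at health services will comprise the health service utilisation outcomes in this study". Data collection places quantitative measurement at T1 (before the programme), T2 (directly after it) and T3 (three months later).

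On the independent t-test and the ANOVA, Data analysis reads: "test will be used to analyse the differences between two groups, while repeated measures ANOVA will be adopted to measure the within-group differences". No covariate is named for the between-group comparison. The section then states "Intervention effects will be reported as model-based means (95% confidence interval [95% CI", but names no between-group model that would produce such means.

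Two procedures bear on the outcome. Under Control group, when a subject voices a health concern or a social problem, "the RA will suggest that the subjects seek help from their general practitioner", although the aim of the contact is described thus: "The purpose of the call will be to control the possible social effects". In the intervention arm, when this is judged necessary, "the NCM will refer the subjects to one of the health and social care team members, such as a general practitioner".

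**The concern.** Past service use is usually a good predictor of later service use. A comparison of follow-up counts that ignores the T1 count leaves stable differences between subjects in the error term, and so widens the confidence interval for no return. With about 29 evaluable subjects per arm the interval is wide already. Utilisation is a named effectiveness objective, and the programme is due to go on to six centres, so a needlessly imprecise estimate carries forward.

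There is a smaller, separate matter. A contact with the trial can itself lead to a GP visit in either arm, by a different route in each. Without a record of which visits arose in this way, a difference in utilisation is harder to interpret.

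**Working it through.** **The plan's own figure.** Sample size: 30 × 1.20 = 36 per group, 72 in total. With 20% drop-out, 36 × 0.80 = 28.8, so about 29 per arm are analysed. The document gives no visit rate, dispersion or baseline correlation, so everything below rests on assumed values.

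**Assumptions.** Counts are gamma-Poisson with mean μ and dispersion k, so Var = μ + μ²/k. The baseline mean is 2 in both arms. The follow-up mean is 2 in controls and 1 in the intervention arm, and k = 1. Let r be the correlation between a subject's propensity at baseline and at follow-up. Then Cov(baseline, follow-up) = r × μ(baseline) × μ(follow-up)/k.

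**Variances.**
- Baseline: 2 + 4 = 6
- Control follow-up: 2 + 4 = 6, covariance with baseline 4r
- Intervention follow-up: 1 + 1 = 2, covariance with baseline 2r

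**Unadjusted t-test.** SE = √[(6 + 2)/29] = 0.525, and 1/0.525 = 1.90. Power ≈ Φ(1.90 − 2.00) = Φ(−0.10) = 46%.

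**Linear ANCOVA.** The common slope is b = [(4r + 2r)/2]/6 = r/2. The residual variance in each arm is V − 2bC + 6b², where V is the follow-up variance and C the covariance.

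| r | b | Residual variance, control | Residual variance, intervention | SE | Approximate power |
|---|---|---|---|---|---|
| 1 | 0.50 | 6 − 4 + 1.5 = 3.5 | 2 − 2 + 1.5 = 1.5 | √(5.0/29) = 0.415 | Φ(2.41 − 2.00) = 66% |
| 0.5 | 0.25 | 6 − 1 + 0.375 = 5.375 | 2 − 0.5 + 0.375 = 1.875 | √(7.25/29) = 0.500 | Φ(2.00 − 2.00) = 50% |

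**Simulation (29 per arm, 2 versus 1 visits, k = 1).** Results agree with the hand calculation to within a few points.

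| Propensity | t-test | Baseline-adjusted |
|---|---|---|
| Stable (r = 1) | 47% | 67–69% |
| r = 0.5 | 49% | 54–55% |
| r = 0.25 | 48% | 49% |

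With k = 0.5, power rises from 29% to 63% (stable) and from 29% to 37% (r = 0.5). With means 1 versus 0.5, k = 1 and stable propensity, it rises from about 35% to 43%.

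**Source of the gain.** With stable propensity and k = 1, linear ANCOVA reached 64% and the overdispersed Poisson model 66%. The covariate does nearly all the work; the count model adds little.

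**Error rates.** With no true difference, the t-test rejected in 4.4–4.8% of trials (30 per arm, means 0.5 to 2, k from 0.5 to 2, 20,000 runs each). Adjusted analyses rejected in 5–6%. The form of the covariate matters: with the raw baseline count in a log-link model, type I error was 6.8% at k = 1 and about 9–10% at k = 0.5.

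**Prompted visits.** If trial contacts add a visits per subject to one arm, the difference in means shifts by a. No figure for a can be derived from the document. Advice in the control arm would push the difference one way, and referral in the intervention arm the other.

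**The case against.** This is a pilot with a rule-of-thumb sample size and no power claim. Effectiveness is described as potential and is measured only if the data can be collected. The reference to model-based means may point to a fuller model in an analysis plan that is not shown. All this is fair and limits the weight of the point. Even so, the article does not leave the between-group method open; it names the t-test, and the T1 data needed for adjustment are planned. The gain also shrinks quickly when past use predicts later use poorly: at r = 0.25 it is about one percentage point.

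A reader might infer something stronger: that the trial itself inflates unscheduled use in controls and so manufactures a benefit. With equal true rates, an assumed 0.25 extra prompted visits per control subject would make the t-test declare a difference in 6–21% of trials. The document does not support that reading as a finding, for four reasons:

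- It does not define unscheduled, so neither an advised GP visit nor a referred one can be classified with confidence.
- Effectiveness is defined against the monthly social call, and the GP suggestion is part of that call; handling concerns through the nurse is part of the programme. Much of the supposed distortion is therefore the contrast under study.
- The advice goes only to subjects who already have a concern, and some would have seen their GP anyway. Prompted visits are not all extra visits.
- Net direction cannot be determined, since referrals may add attendances in the intervention arm.

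Nor can the t-test be blamed for distortion, since its error rate is near nominal.

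**Conclusion.** The point holds as one of precision, not bias. The plan fixes an unadjusted comparison of utilisation although the baseline count is planned, and adjustment costs no extra subjects. Under the assumed rates at k = 1, power rises by about 20 percentage points if propensity is stable and by about 5 if propensities correlate at 0.5. The gain depends on visit rate, dispersion and stability over time, none of which the document gives, and on the T1 count covering a period comparable with follow-up.

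The differing routes to a GP visit are a matter of interpretation: part of any difference may reflect the advice given within the comparator, with unknown size and direction. The document does not show that the contrast is biased.

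**What to change.** 1. Analyse utilisation at T2 and at T3 with group and baseline utilisation in the model. Linear ANCOVA is sufficient. If a rate ratio is preferred, use an overdispersed Poisson model with log(baseline count + 0.5) as covariate, not the raw count. Report the adjusted difference or rate ratio with its 95% CI.
2. Mark visits that followed the control caller's suggestion or a nurse referral, using the trial's call and referral records. Link these only after the outcome interview: the research assistant who collects outcomes is blinded, and asking subjects what led to a visit would reveal the arm.
3. Report the marked visits descriptively by arm. Keep every visit in the main intention-to-treat comparison, because removing visits by an arm-specific cause arising after randomisation would break the randomised comparison.
4. Leave the advice and referral rules as they are.

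The cost is slightly more analysis work and some record linkage, which presumes that control calls and referrals are logged. No additional subjects or interview questions are needed.
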